### Ethics and dissemination

The study protocol has been reviewed and approved by the Makerere University School of Public Health Research and Ethics Committee (SPH-REC), College of Health and Sciences, Uganda, and cleared by the Uganda National Council of Science and Technology as per national research regulations. Any protocol modifications will be submitted to the SPH-REC for review, and participants will be informed if warranted. The trial is registered with the NIH clinical trial registry (clinicaltrials.gov) and assigned the number NCT04960748 (registration date: June 25, 2021). To ensure and maintain the scientific integrity of this human subject research project, and to protect the safety of its research participants, we will have a single, independent monitor (a reproductive health research scientist at the Makerere School of Public Health) to intermittently monitor study results and adverse event data (at months 3 and 6 of implementation of the intervention). The monitor will be provided with periodic reports which include subject enrollment, subject retention, reasons for dropping out, and a listing of all adverse events that are plausibly related to the intervention or study procedures. Adverse events that are considered directly related to the intervention or other aspect of study participation will be reported immediately to the monitor, the IRBs, and NIH. After review of the periodic reports, the monitor will make a recommendation regarding the continuation, modification, or termination of the study. All communications from the independent monitor will be shared with the IRBs and NIH.

As a first step for dissemination, reporting results will be documented on ClinicalTrials.gov in accordance with NIH requirements on dissemination of clinical trial results. Information submitted will occur no later than 12 months after the primary completion date. Results produced by this investigation will be presented at international conferences and published in a timely fashion, ideally in the last year of the study period. All final peer-reviewed manuscripts that arise from this proposal will be submitted to the digital archive PubMed Central for open access. De-identified data, assessment and intervention materials, and analytic code will be made available upon request from external researchers and following review and approval of the study team.

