## Methods

### Study design

This study will pilot test a social network-based group intervention that aims to empower and mobilize women who have been screened for CC to advocate for CC screening and treatment in female members of their social network (referred to as “alters”). We will pilot the intervention in a randomized controlled trial of 40 women who have been screened for CC (referred to as index participants), with 20 randomly assigned to receive the intervention (in two groups of 10) and 20 to the wait-list control [(each evenly stratified by age (under and over age 35) and history of CC-related treatment)]. Individual randomization entails risks for contamination, but statistical models suggest that ≥ 30% of the control arm must receive the equivalent of a full-strength intervention to result in meaningful contamination [24]. We opted for the wait-list control rather than an attention control, because this provides clearer findings for policy makers when considering intervention effects, and adequate control for attention may not be feasible given the 2-h duration and group dynamics of the workshops. The control arm receives the intervention after the completion of month-6 follow-up assessments. There is no way to blind the participants on whether or not they receive the intervention; this could potentially influence the outcomes, as clients may feel more or less incentivized to perform well in light of whether or not they receive the intervention. We do not see a way to prevent this potential bias, nor a way to distinguish such effects from actual intervention effects, but this limitation will be cited in reports of study findings. Data will be collected at baseline and month 6 from index participants and up to three alters of each index participant (max. total = 120 alters) who have not previously screened for CC. The primary outcome is alter CC screening over the 6-month follow-up period; secondary outcomes are index participant reported engagement in CC screening advocacy, internalized CC stigma, and disclosure of CC screening experience.

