### Participants

Women are eligible to enroll as index participants if they are age 18 years or older, have screened for CC within the past year, have stable health status (i.e., not in end stages of disease), and shared their CC screening experience with at least one alter who is perceived to not have screened for CC in the past 3 years. Alter participants are eligible if they are at least 18 years of age, are recruited by an index participant, and report never being screened for CC.

Index participants will be recruited through the RHHJ database of women who have received CC screening and referral from Buyinja and Banda providers who have screened women for CC. An RHHJ staff member or health center provider will inform eligible women of the study, and those who express interest in participating will be referred to the study coordinator for formal eligibility screening and implementation of consent procedures. Women who provide written informed consent will then be administered the baseline assessment and be randomly assigned to the intervention or control arm. To recruit alters, we will use data collected from the baseline survey assessment of female social network members to randomly select 5 alters who know the participant’s CC screening experience (or as many as there are if < 5) and ask the participant if she is comfortable asking 3 of these alters to participate. The index participant will be asked to call each selected alter at the end of the interview to describe the study in the presence of the coordinator, who will schedule a study visit for alters who express interest in participating. If an alter refuses or cannot be reached, a replacement will be randomly selected from the list of alters who know the index participant’s CC screening experience.

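### Both adverse event reporting rules select on judged relatedness and neither on seriousness: events judged unrelated are not listed, harms cannot be fairly compared by arm, and a serious, only plausibly related event could wait about 3 months

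*Protocol article*

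**What the plan says.** All the reporting rules are in the protocol article, Ethics and dissemination. A single independent monitor is "to intermittently monitor study results and adverse event data (at months 3 and 6 of implementation of the intervention").

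- **Periodic reports.** These include enrollment, retention, reasons for dropping out, and "a listing of all adverse events that are plausibly related to the intervention or study procedures".
- **Immediate reports.** "Adverse events that are considered directly related to the intervention or other aspect of study participation will be reported immediately to the monitor", and also to the IRBs and NIH.
- **Use of the reports.** "After review of the periodic reports, the monitor will make a recommendation regarding the continuation, modification, or termination of the study".

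Four statements elsewhere bear on how these rules work:

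- Study design: "The control arm receives the intervention after the completion of month-6 follow-up assessments".
- Study design, on masking: "There is no way to blind the participants on whether or not they receive the intervention".
- Participants: index women in both arms must already have shared their screening experience with at least one network member. On recruiting alters, "The index participant will be asked to call each selected alter at the end of the interview to describe the study".
- Introduction: the article recognises that disclosure can bring rejection, ridicule or shame.

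**The concern.** The two rules are stated, so this is not a complaint about missing detail. Each makes reporting depend on a judgement of cause that precedes the monitor's sight of the event, and neither uses seriousness.

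One consequence is for the comparison of harms. Conflict or rejection after a woman talks about her screening can occur in either arm, since women in both arms have already disclosed to someone. In the intervention arm such an event can be tied to the workshops or to study procedures. In the control arm, before month 6, it can be tied only to study procedures. If it is judged unrelated it is not listed, and the monitor cannot question a causality call on an event not shown. The recommendation to continue, modify or stop follows review of these reports.

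The other consequence is for timing. Urgency is sorted by how certain the cause is, not by how grave the event is. A minor event judged directly related goes out at once, while a serious event judged only plausibly related has no immediate route in the printed text. The cause of a social harm is seldom certain, so such harms may well fall in the second group.

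**Working it through.** The plan gives no figure to reproduce here. The check is a reading of the two rules side by side, plus interval arithmetic.

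**Step 1. Where each kind of event goes under the printed rules**

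| Event, as judged | Immediate report | Periodic listing |
|---|---|---|
| Directly related, minor | Yes | Yes |
| Directly related, serious | Yes | Yes |
| Plausibly but not directly related, minor | No | Yes |
| Plausibly but not directly related, serious | No | Yes |
| Unrelated, minor or serious | No | No |

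The minor and serious rows always give the same answer, so seriousness changes nothing in either rule. (The table takes a directly related event to be plausibly related as well.)

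**Step 2. Does either rule exclude an arm?** No. The listing covers events related to the intervention *or* to study procedures, and the immediate route covers the intervention *or* any other aspect of participation. Control index women and their alters are interviewed, have their charts abstracted and take part in the recruitment calls. Their events can meet either rule.

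**Step 3. Does the filter fall equally on the two arms?** Let the same background event occur equally often in both arms. Write *a* for the chance that it is judged plausibly related to study procedures. Write *b* for the chance that it is not, but is judged plausibly related to the workshops.

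- Intervention arm, share listed: *a* + *b*
- Control arm before month 6, share listed: *a*, because there are no workshops to relate it to

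The difference is *b*, which is zero only if no background event is ever attributed to the workshops. This needs no assumption that the causality assessment is biased. The documents give no event rate and no attribution rate, so *a* and *b* cannot be given values, and only the direction is established.

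**Step 4. Longest wait for a plausibly but not directly related event.** The reviews are at months 3 and 6 of implementation.

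- Start to first review: 3 − 0 = 3 months
- First to second review: 6 − 3 = 3 months

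An event just after the start, or just after the month-3 report, could therefore wait up to about 3 months. The Intervention section runs the seven workshops over 2 months. If implementation is counted from the first workshop, a group that starts then has finished about 3 − 2 = 1 month before the first review.

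**Step 5. Size of the listing if the filter is removed.** It would cover 40 index women and up to 120 alters: 40 + 120 = 160 women at most.

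**The case against.** Five counter-arguments deserve a fair hearing.

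1. **Control events are covered.** A reader might infer that control-arm events drop out of the listing altogether. The text does not support that. Step 2 shows that neither rule is limited by arm, and conflict following a recruitment call could be listed for a control woman. What is lost is any event judged unrelated, in either arm, so the listing is uneven rather than one-sided. This objection stands.

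2. **No biased judgement is shown.** The masking statement concerns participants. The article does not say who judges relatedness or whether that person knows the arm. A reader might infer that the assessor will favour one arm, but nothing printed establishes it. The objection stands as far as it goes, but Step 3 does not depend on bias.

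3. **Plausibly related is a low threshold, and there are backstops.** Doubtful social harms would often meet it. The reports also carry reasons for dropping out, they are said to include the listing rather than consist of it, and the monitor's remit is adverse event data in general. This narrows the loss. It does not remove it, because the only event listing described is the filtered one.

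4. **The article condenses a fuller protocol.** Serious-event timelines and ethics committee procedures may be set out there, so their absence from the article is no finding. That is correct, and it is why the 3-month wait is conditional. It does not cover the two rules that the article does state.

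5. **Complete counts would decide little.** With 20 index women per arm, even full data could hardly show an excess of harms. This is fair as to formal comparison. The monitor's task is also to read individual events, and the pilot is meant to inform a larger trial, for which unfiltered counts by arm are useful.

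**Conclusion.** The point holds in limited form. As printed, both rules select on relatedness and neither on seriousness.

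- **Arm comparison.** Events judged unrelated are not listed in either arm. Because only one arm has workshops before month 6, the filter falls unevenly, and the listing cannot support a fair comparison of harms by arm. The direction follows from the design. The size cannot be derived, because any count of listed events per arm would rest on assumed event and attribution rates.
- **Timing.** A serious event judged only plausibly related could wait up to about 3 months. This assumes that reports reach the monitor only at the two stated reviews and that no serious-event rule in the full protocol applies.

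This is a cheap improvement to safety oversight. It is not an internal contradiction, and it does not show that events would be concealed or misjudged.

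**What to change.** Amend the two rules in Ethics and dissemination.

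- **Periodic report.** List all recorded adverse events and social harms in index and alter participants, by arm, whatever their judged cause. Show the team's causality call as a column that the monitor can query.
- **Immediate report.** Keep the present route for directly related events. Add immediate reporting of serious events that are at least plausibly related, aligned with any serious-event rule in the full protocol.

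The new trigger should be added to the existing one, not put in its place. Replacing it would move non-serious but directly related social harms, which now go out at once, to the periodic report.

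The cost is a wording change and a somewhat longer listing that includes unrelated events, for at most 160 women. No extra visits are needed.

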## Discussion

This study will conduct a randomized, controlled pilot evaluation of a social network-based group intervention designed to empower women who have screened for CC to advocate for CC screening and early treatment among women in their social networks. To our knowledge, no published study has used a network-driven approach and empowerment of screened women (some of whom have also been treated for CC risk) as change agents to increase CC screening and treatment, let alone in Africa. This is one of the few network-driven interventions to use social network data not only to evaluate effects on the behavior of network members but also to inform intervention strategies for targeting advocacy to bridging and popular network members, which may optimize the knowledge and support transfer for CC protective behaviors throughout a network. With essentially every family affected by CC risk in high-prevalence settings like Uganda, the intervention can dramatically impact the mortality and morbidity of CC through widely disseminated and targeted advocacy. This study will inform a future, larger controlled intervention trial, including a more extensive evaluation of effects on network members and the community. If successful, this intervention model has the potential to not only impact uptake of CC screening and treatment but also to establish a paradigm that can be applied to other health conditions.

## Data Availability

This is a protocol paper, and no data are available yet. De-identified data, assessment and intervention materials, and analytic code from this study will be made available with subsequent papers.
